#### Quantitative component

We chose a prospective cohort design to investigate primary and secondary outcomes, incorporating use of standard measures for psycho-social outcomes (e.g. the Edinburgh Depression Scale and Modified Kessler Psychological Distress Scale - K5). Selecting comparison cohorts from the same sites in earlier years for data-based analyses reduces the potential for selection bias. We will describe the general characteristics of women in each cohort to establish comparability.

#### Qualitative component

Multiple qualitative methods and data sources will be used including yarning interviews and yarning circles [50, 51], free text responses in participant surveys, the project log and field diaries/notes, and minutes from meetings. We will also specifically investigate the experiences of women accessing the Waminda Empowering Mothers’ and Babies’ Autonomy (EMBA) process that offers integrated, wraparound multidisciplinary support for First Nations women and families managing complex life circumstances in pregnancy.

#### Cost-effectiveness component

The health economic evaluation will take a health system perspective and conduct a cost-effectiveness analysis from women’s first antenatal visit until 6 weeks after birth. The following costs will be included: antenatal care, birth services, postnatal care, readmissions within 6 weeks postpartum, infants’ special care nursery and readmission within 28 days post birth. The mean cost of care per mother/infant pair will be calculated. The personnel cost including midwife and obstetrician will be estimated using their hourly rate plus on-costs. The costs of diagnostic tests and investigations will be estimated from the government Medicare Benefits Schedule (MBS) and pharmaceuticals from the Pharmaceutical Benefits Schedule (PBS). All hospital admission costs will be based on Australian refined Diagnostic Related Groups (DRGs).

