### Study components

Using quantitative and qualitative research methods; including clinical and cost-effectiveness data, surveys including questionnaires with validated tools and open response items, interviews, yarning circles and field notes, we will ascertain:Maternal and infant health outcomes (effectiveness): for women obtaining maternity care through *Minga Gudjaga* (Mother & Baby) at Waminda or through BiOC North at IUIH. Routinely collected mother and baby clinical outcomes will enable service effectiveness analysis from commencement of the new service compared with baseline data (standard care) for both sites.Service acceptability: maternal surveys will be undertaken at three time points; approximately 36 weeks antenatally, 2 and 6 months postnatally (see Table 2 & Additional File 2 indicating scales and tools used). A qualitative research component will explore pregnancy, birthing, postnatal and early parenting experiences of a subset of women and will explore cultural safety.Services feasibility, cost-effectiveness and sustainability: Staff and key stakeholder perspectives and experiences will be gathered and will incorporate workforce issues when analysing feasibility and sustainability. A cost-effectiveness analysis of care from the first antenatal visit until 6 weeks after birth will be undertaken by extracting and comparing data on service items, health conditions and diagnoses (therefore procedures and treatments).

**Table 2 Tab2:** Summary of secondary outcome measures, data collection time points and tools

*#*	*Outcome*	*Method of data collection*	*36 weeks*	*At birth*	*2 months*	*Between 2 & 6 months*	*6 months*
*Cultural safety outcomes*							
1	**Women’s cultural safety views and experiences**	SUR QUAL			X	X	
2	**Women’s experiences of (dis)respect**	SUR QUAL			X	X	
3	**Women’s experiences of discrimination/racism**	SUR QUAL	X		X	X	
*Maternal outcomes during pregnancy, birth and the postnatal period*							
4	**Women’s feelings of control during labour and birth** (rated on a 0–10 scale)	SUR QUAL			X	X	
5	**Smoking status at first antenatal visit** (yes/no)	SUR MEDREC	X (At first AN visit, < 20 weeks, 20 + 1 wks - birth)	X	X		
6	**Experienced continuity of care** measured with 3 subscale scores of the Nijmegen Continuity Questionnaire (NCQ) pregnancy adaptation	SUR QUAL			X	X	
7	**Pharmacological analgesia in labour** (regional [epidural/spinal] and/or narcotic analgesia, nitrous oxide gas)	MEDREC		X			

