8	**Onset of labour** (induced, no labour, spontaneous)	MEDREC		X			
9	**Augmentation of labour** with artificial oxytocin	MEDREC		X			
10	**Place of birth** (e.g. home, birth centre, hospital)	MEDREC		X			
11	**Mode of birth** (non-instrumental vaginal birth, instrumental vaginal birth, caesarean section)	MEDREC		X			
12	**Water birth** (yes/no)	MEDREC		X			
13	**Perineal status** (intact/1st degree tear, 2nd degree tear, 3rd/4th degree tear)	MEDREC		X			
14	**Episiotomy** (yes/no)	MEDREC		X			
15	**Management of third stage labour** (active, physiological)	MEDREC		X			
16	**Postpartum hemorrhage** (blood loss < 500; 500–999; 1000–1499; 1500 ml and/or with blood transfusion	MEDREC		X DC – 6 wks			
17	**Mother admission to hospital** up to 6 weeks postpartum (yes/no)	MEDREC		X – 6 wks			
18	**Women who had a known midwife in labour and/or birth** (yes/no)	SUR			X		
19	**Birthing and maternity care experiences**	SUR QUAL	X		X	X	X
20	**Maternal parenting self-efficacy**	SUR QUAL			X	X	
*Fetal, neonatal and infant outcomes*							
21	**Low birth weight** (< 2500 g, 2500 g or more)	MEDREC		X			
22	**Birth weight** (grams, mean, sd)	MEDREC		X			
23	**Apgar score 5 minutes** (< 7, 7 or above)	MEDREC		X			
24	**Admission to a separate neonatal nursery** (yes/no)	MEDREC		X - DC			
25	**Breastfeeding status at 2 and 6 months postpartum** (exclusive, mixed, formula only, other)	SUR			X		X
26	**Infant admission to hospital up to 28 days of age** (yes/no)	MEDREC		X – 28 days			
27	**Length of facility stay for mothers and infants following birth** (mean, median, range)	MEDREC		DC			
*Social & Emotional Wellbeing outcomes/variables, Culture and Connection*							
28	The **Edinburgh Postnatal Depression Scale** (EPDS) score (could also be assessed at other timepoint(s) as clinically indicated)	MEDREC SUR	First AN visit		X		X
29	**Negative Life Events Scale** (NLES) (full extended version) score	SUR	X				X
30	The **modified Kessler psychological distress scale** (K5) score	SUR	X		X		X
31	**Women’s cultural connection and identity**	SUR QUAL	X			X	X
*Acceptability, safety and satisfaction*							
32	The **feasibility and acceptability of an established Birth Centre** assessed by the proportion of eligible women in Birthing on Country care who start labour in the birth centre	MEDREC QUAL		X		X	
33	The **proportion of women who transferred from the birth centre**/model of care at any time and for any reason	MEDREC		X DC			
*Cost outcomes*							

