34	**Mean cost of care per mother/infant pair** Health economic evaluation takes a health system perspective and will conduct a cost-effectiveness analysis. Costs to be included are antenatal care, birth, postnatal care costs; readmissions costs within 6 weeks postpartum; infants’ special care nursery and readmission.		First AN visit	Until 6 weeks (mother) 28 days (baby)			

Key: *DC* Discharge (from hospital/birth centre etc), *MEDREC* Medical/maternity/obstetric records, *QUAL* Qualitative data collected via audio recorded, one-to-one yarns (a type of narrative interviewing), unstructured/semi-structured interviews, yarning circles (a type of focus group discussion), researcher field notes, *Sd* Standard deviation, SUR Questionnaires (surveys) designed for this study, *Wk* week

Notes

1. All tools/scales will be scored according to their recommended guidelines and outcomes reported accordingly

2. All items measured for both intervention and standard care groups

3. The time period under consideration for the innovation is from the first day of pregnancy until handover to child health services at 6 weeks postpartum, however the study is longitudinal following mothers and babies until 6 months

4. Please see Additional File 2 for more detail on scales and tools used in women’s surveys

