#### Power and sample sizes

BOOSt has been powered to detect a clinically significant change in preterm birth [53]. Preterm birth rates for First Nations babies in the Illawarra Shoalhaven Local Health District have been reported over a recent 5 year period as between 10.3 and 17.5%, average 12.9%. Based on our observations in the IBUS study [19], we propose a minimum treatment effect of 50% reduction (Odds ratio OR 0.5) for the preterm birth rate in the innovation arm. During recruitment, we will aim to access routinely collected maternity data for approximately 687 women at the rural site and 614 from the urban site (based on an estimated 20% attrition rate). From commencement of the new model of care, we will aim to obtain data from a minimum of 296 births (rural site) and 264 (urban). Given small numbers in the rural site (~ 120 births of First Nations babies attending Birthing on Country per year) and a ~ 3.5 year post-intervention study timeframe, we estimate 70% of the total sample to be in the pre-intervention group and 30% post-intervention. To detect this difference with 80% power and a type 1 error of 5%, and factoring exclusions for ~ 7% twin babies/babies with fetal anomaly, and 10% missing data, 983 women/births in total are needed, which includes 687 in pre-intervention and 296 in post-intervention groups. This sample size will also enable enough power for primary infant and maternal outcomes. For the urban site, the required sample size would be 878: 614 in pre-intervention and 264 in post-intervention groups. For the sub-studies, the sample size will be determined according to qualitative research conventions and considerations around data saturation.

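### Infant costs stop at 28 days in a cost-effectiveness analysis stated to run to 6 weeks, so one mean cost per mother/infant pair mixes two horizons

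*Protocol article*

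**What the plan says.** The horizon is given twice in the protocol article. Under Study components: "A cost-effectiveness analysis of care from the first antenatal visit until 6 weeks after birth will be undertaken". Under Cost-effectiveness component, the evaluation will "conduct a cost-effectiveness analysis from women’s first antenatal visit until 6 weeks after birth".

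The infant items are then given a shorter window. The list of costs under Cost-effectiveness component ends with "infants’ special care nursery and readmission within 28 days post birth". Table 2, item 34 (the cost outcome), gives the time window as "Until 6 weeks (mother) 28 days (baby").

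The two windows are combined in one result: "The mean cost of care per mother/infant pair will be calculated".

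Three other statements bear on the point:

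- The costing basis: "All hospital admission costs will be based on Australian refined Diagnostic Related Groups (DRGs").
- Table 2, item 26, a clinical outcome with the same 28-day limit: "Infant admission to hospital up to 28 days of age".
- Table 2, note 3, which says that the innovation runs to handover to child health services at 6 weeks and that mothers and babies are followed to 6 months.

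**The concern.** A mean cost per mother/infant pair is meant to describe one unit over one period. Here the mother contributes costs to day 42 and the baby to day 28. An infant readmission on day 35 falls within the declared horizon, and within the period that the protocol assigns to the innovation, but does not enter the result.

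The gap need not cancel between cohorts. Under Power and sample sizes the article states: "BOOSt has been powered to detect a clinically significant change in preterm birth", with an assumed odds ratio of 0.5. If late infant costs arise more often after preterm birth, they arise more often in the cohort with more preterm births, and leaving them out shrinks the cost difference between cohorts. The Abstract says that costs will be reported to policy advisors and used for scale-up, so the figure will have readers who take the 6-week horizon at its word.

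**Working it through.** **Step 1. The windows side by side**

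| Place in the protocol article | Mother | Baby |
|---|---|---|
| Study components (horizon of the analysis) | 6 weeks | 6 weeks (no separate limit) |
| Cost-effectiveness component (horizon) | 6 weeks | 6 weeks (no separate limit) |
| Cost-effectiveness component (list of costs) | 6 weeks for readmissions | 28 days |
| Table 2, item 34 (time window) | 6 weeks | 28 days |

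The horizon statements and the infant items disagree. The disagreement appears both in the text and in the table.

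**Step 2. Size of the gap in time**

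6 × 7 = 42 days; 42 − 28 = 14 days; 14/42 = 33% of the postnatal horizon. On every reading, infant readmissions on days 29 to 42 are left out.

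**Step 3. Does the 28-day limit also cut the birth admission?**

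The text does not settle this.

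- For a cut: the time cell of Table 2, item 34, gives 28 days for the baby without restricting it to readmissions.
- Against a cut: in the list of costs, the limit can attach to readmission alone. The cost list inside item 34 puts no limit on nursery care. Admissions are costed by DRG, which works by episode. Table 2, items 24 and 27, record nursery admission and length of stay to discharge.

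**Step 4. What a literal cut would do to single babies (illustration only)**

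The documents give no nursery stays. Assume discharge at 36 to 37 weeks' postmenstrual age. For a birth at g weeks and discharge at D weeks, stay = (D − g) × 7 days, and the share beyond day 28 = (stay − 28)/stay.

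| Birth at | D = 37: stay, share beyond day 28 | D = 36: stay, share beyond day 28 |
|---|---|---|
| 28 weeks | 63 days, 35/63 = 56% | 56 days, 28/56 = 50% |
| 30 weeks | 49 days, 21/49 = 43% | 42 days, 14/42 = 33% |
| 32 weeks | 35 days, 7/35 = 20% | 28 days, none |

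A stay passes day 28 only if g < D − 28/7, that is, before 33 weeks (D = 37) or 32 weeks (D = 36). With a 42-day limit the corresponding points are 31 and 30 weeks, so moving the limit to 42 days would still cut the earliest births: (63 − 42)/63 = 33% of a 63-day stay.

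**Step 5. Effect on mean cost per pair**

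This needs unit costs, readmission rates on days 29 to 42, lengths of stay and the distribution of gestation at birth. The document gives none of them. It gives an average preterm rate of 12.9% for the rural district, and births before 32 to 33 weeks are only a part of that. No cost figure can be derived.

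**The case against.** The strongest reply is that the 28-day infant window is deliberate. It is stated openly in two places, agrees with clinical outcome 26, and touches one secondary outcome and no power figure. How a stay that crosses a cut-off is costed is also a detail that an article commonly leaves to the full protocol or an economic analysis plan.

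Much of this stands. The primary comparisons are unaffected, and the handling of stays that cross day 28 is not faulted as a missing detail. The horizon mismatch remains, because the article itself fixes both windows and gives no reason for the shorter one. A 28-day limit that suits a clinical readmission outcome does not thereby suit a cost horizon declared as 6 weeks.

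A reader might go further and infer that the plan truncates long nursery stays and so drops 20% to 56% of nursery days for early preterm babies. The document does not support that as a statement of fact. The wording can confine the limit to readmission, DRG costing may capture the whole birth admission, and the percentages rest on an assumed discharge age. They describe individual babies and do not measure bias in the mean cost per pair. Nor does the document show that preterm babies carry most of the late neonatal cost.

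**Conclusion.** The point holds in a limited form. The cost outcome does not match its own stated horizon: infant readmissions on days 29 to 42, one third of the 42 postnatal days, are not costed, while the mother's costs run to day 42. Truncation of the birth admission is possible under a literal reading of Table 2, item 34, but is not established.

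The likely direction is an understatement of savings. This assumes that the service lowers preterm birth and that infant costs after day 28 are more frequent after preterm birth. Under those assumptions the error works against the service rather than for it. The size in money is unknown and cannot be derived from the document. The change is worth making because it is cheap, but it is a moderate matter confined to a secondary outcome.

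**What to change.** - Count infant readmissions to 42 days, so that mother and baby share the stated horizon.
- Cost the whole birth admission, including nursery care, as one episode to discharge. State this as an explicit exception to the 42-day limit, since some stays may pass it.
- Keep 28 days only for clinical outcome 26 in Table 2.
- Amend the list of costs under Cost-effectiveness component and the time window of Table 2, item 34, to match.

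The cost is 14 more days of infant admission data from the same databases, and a wording change in two places.

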### Outcome measures

#### Primary maternal outcomes

First antenatal visit^3^ in the first trimester (< 14 weeks) [for definition please see p. 5 [52]]Total number of antenatal visits (either 0–4, or > =5)Normal birth (> = 37 weeks, vertex presentation, spontaneous onset of labour, no regional analgesia, spontaneous vaginal birth, no episiotomy)

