Workforce strategy	No specific pathways to support First Nations MIH workforce.	Supportive career pathways with First Nations MIH workers embedded in the team with cadetships (or similar) to support midwifery education for First Nations persons. Aboriginal Family Support Workers (or similar) work side-by-side with midwives.
Continuity	No continuity of midwifery carer through antenatal, intrapartum and postnatal continuum. Care is fragmented and women see multiple providers.	Continuity of midwifery carer networked from community to a higher-level service, offering 24/7 care from a named midwife from first presentation in pregnancy until handover to child health services 6 weeks after birth. Midwifery Group Practice (caseload) midwife providing clinical care in collaboration with the extended workforce based on need (e.g. psychologist, social worker, obstetrician, paediatricians, sexual and reproductive health).
Strengthening family capacity	No maternity programs focussed on strengthening family capacity and/or cultural connection in relation to services offered through this hospital. Women may enrol in external programs.	Programs that focus on strengthening family capacity and cultural connection in relation to MIH, integrated with the BoC service.
Place of birth	No out-of-hospital option. Hospitals do not recognise or incorporate the knowledge, values and birth aspirations of First Nations people.	During the first and second phase of the new care model, all intrapartum care will occur in hospitals. If feasible, a free-standing, community-based birth centre will be set up and available for First Nations women with uncomplicated pregnancies (Category A according to consultation and referral guidelines) [18]; women with complex pregnancies (Category B or C) will birth in the local or tertiary hospital. Birth care will incorporate traditional practice; recognise the connection with Land and Country; incorporate holistic health; value both First Nations and non-First Nations ways of knowing, learning and risk assessment; and will provide a culturally competent service.

Note: *MIH* Maternal and Infant Health

^a^Some sections reproduced from Kildea, Gao et al. [19] Permission not required under licence CC BY-NC-ND 4.0

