### Study participants & eligibility

#### Inclusion/exclusion criteria

##### Cohort study

Routinely collected data will be extracted for all women within the historical and intervention time periods who gave birth (or were booked to give birth) to a First Nations baby in the study sites (2013–2022). Exclusions will be based on standard and/or previously used methods to ensure validity and rigour.

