#### Quantitative data

##### Health services and other routinely collected data

Anonymous data from all women attending the site hospitals and health services during the study period will be extracted and analysed by birth model of care. Quantitative analyses will compare maternal and infant health outcomes between the baseline cohort (both sites) and Birthing on Country service innovation cohort (both sites), as well as standard care/concurrent and historical control groups, and non-First Nations groups (where available).

The clinical and costing outcomes data will be derived from routinely collected electronic healthcare databases at each site. Data will be imported to Stata® or Statistical Package for Social Sciences (SPSS®). While data will initially be re-identifiable (with unique study number) all patient identifiers will be removed. Data cleaning and coding decisions will be documented.

Analysis will be performed with the latest version of the appropriate software and statistical significance will be determined at the 0.05 level. Binary outcome measures will be presented using odds ratios with 95% confidence intervals. Several methods will be used to address selection bias e.g. multivariate logistic regression models, linear regression models, propensity score matching (identifies and controls for confounders e.g. the presence of pregnancy complications), and multilevel modelling controlling for clustering factors. Longitudinal outcomes will be analysed with generalized estimating equations to account for the correlation between observations repeated in the same person. We will use trend analysis to compare rates of preterm birth between First Nations and non-First Nations women, which will demonstrate if this inequity has reduced.

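### Two primary antenatal-visit outcomes are tied to entry into the service, yet women who attended it are compared with a baseline of all women who gave birth or were booked

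*Protocol article*

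**What the plan says.** The protocol article lists three primary maternal outcomes (Primary maternal outcomes). The first is a first antenatal visit "in the first trimester (< 14 weeks"). The second is "Total number of antenatal visits (either 0–4, or > =5"), so a woman with no visit at all falls in the lower category.

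Table 1 describes care from the new service as running "from first presentation in pregnancy until handover to child health services 6 weeks after birth". Exposure therefore starts at a first contact.

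The innovation group is made up of service users. Study components assesses effectiveness for women who obtain care through the two new services, against standard-care baseline data. Power and sample sizes counts about 120 attending births a year at the rural site. Under Health services and other routinely collected data, records "will be extracted and analysed by birth model of care".

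The source population is wider. The Cohort study criteria cover 2013–2022 and take in "all women within the historical and intervention time periods who gave birth (or were booked to give birth"), where the baby is First Nations and the site is one of the two under study.

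On selection, Quantitative component states: "Selecting comparison cohorts from the same sites in earlier years for data-based analyses reduces the potential for selection bias". The analysis section adds regression, propensity score matching and multilevel models. Concurrent standard-care controls are used where available.

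Outcome 5 in Table 2 is titled "Smoking status at first antenatal visit", though its row also lists later time points.

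**The concern.** For these two outcomes, being in the innovation group depends partly on the outcome itself.

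A woman who has no antenatal visit, or who first presents in labour, counts as a failure in the historical group. After launch she cannot be a service user, so she is missing from the innovation group. Gestation at first visit is already settled when the service takes a woman on, so a difference among attenders may show only which women entered.

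Taking controls from the same sites in earlier years does not help, because the selection happens in the later period. Regression and propensity scores balance measured covariates between the women who are present. They cannot restore women whom the group definition leaves out.

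At stake is whether a favourable result on two primary outcomes, meant to inform policy and scale-up, can be read as an effect of the service.

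**Working it through.** **Group sizes.** The protocol gives no rates, power or sample size specific to the visit outcomes. Its rural sample size for preterm birth supplies the group sizes and can be reproduced. With 12.9% versus 6.45%, two-sided 5%, 80% power and a 70:30 split, the usual two-proportion formula without continuity correction gives 572 + 246 = 818. Allowing for 7% exclusions and 10% missing data, 818/(0.93 × 0.90) = 978, or 818/0.83 = 986. The stated 983 (687 + 296) lies between. After those losses the sizes are 687 × 0.837 = 575 and 296 × 0.837 = 248.

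**Visit count, no service effect.** Let *p* be the share of controls with five or more visits and *u* the share of controls who could never enter the service. All of the latter have fewer than five visits. If attenders otherwise resemble controls, their rate is *a* = *p*/(1 − *u*). The values of *p* and *u* are assumptions. With *p* = 0.85, the control odds are 0.85/0.15 = 5.67.

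- *u* = 2%: *a* = 0.85/0.98 = 0.867; odds ratio = (0.867/0.133)/5.67 = 1.15.
- *u* = 5%: *a* = 0.85/0.95 = 0.895; odds ratio = (0.895/0.105)/5.67 = 1.50.

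The chance of a spurious favourable result is Φ[(*a* − *p* − 1.96 × SE₀)/SE₁], where SE₀ uses the pooled rate and SE₁ the separate rates. The nominal value is 2.5%.

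- 687 vs 296, *u* = 2%: (0.0173 − 1.96 × 0.0245)/0.0240 = −1.28, giving 0.10.
- 687 vs 296, *u* = 5%: (0.0447 − 1.96 × 0.0239)/0.0224 = −0.09, giving 0.46.
- 575 vs 248: 0.09 at *u* = 2% and 0.40 at *u* = 5%.

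Range of assumptions at 575 vs 248:

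| *p* | *u* = 1%: OR (chance) | *u* = 3%: OR (chance) | *u* = 5%: OR (chance) |
|---|---|---|---|
| 75% | 1.04 (4%) | 1.14 (10%) | 1.25 (22%) |
| 85% | 1.07 (5%) | 1.25 (16%) | 1.50 (40%) |
| 90% | 1.11 (6%) | 1.43 (23%) | 2.00 (62%) |

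**First-trimester visit, no service effect.** Let *e* be the share presenting before 14 weeks, and let late presenters enter the service at *r* times the rate of early presenters. Attenders then show *e*/(*e* + (1 − *e*)*r*), and the odds ratio is 1/*r*. With *r* = 0.75 it is 1.33, and the chance of a spurious favourable result is 38% to 47% for *e* between 70% and 50%. With *r* = 1.25 it is 1/1.25 = 0.80, against the service. The protocol does not fix *r*, so neither size nor direction is known.

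**Room for selection.** 120/453 = 26%: the expected rural service births set against First Nations births in the wider Illawarra Shoalhaven area in 2018. The catchments differ, so this is indicative only.

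**The case against.** A reader might infer that both visit outcomes favour the new service by construction. The documents do not support that. A continuity service can genuinely raise the number of visits, so only the zero-visit and very late tail is structurally one-sided. For first-visit timing, a community-governed service may bring women into care earlier, and the rural service also supports women with complex life circumstances, so selection could run either way. The footnote and cited definition behind the first-visit outcome are not in the text at hand, so the visit might be with another provider. A visit elsewhere before joining would still precede the service.

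A reader might also infer that outcome 5 can show no effect of care on smoking. It can: its row lists smoking before 20 weeks, from 20 weeks to birth, at birth and at 2 months. Only the first-visit value is a pre-service measure, and the outcome is secondary.

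The protocol also says exclusions will follow standard or previously used methods. These might remove zero-visit women from the baseline, but the text does not say so, and removing them would leave selection on late presentation. Concurrent standard-care controls do not cure the problem either, since women who never reach the service fall into that comparator.

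Finally, the visit rates are assumed. That is correct, and the figures are illustration only.

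**Conclusion.** The point holds in a limited form. The protocol itself fixes both the grouping by care received and the two outcomes, and the planned adjustment methods cannot undo the dependence between them.

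- **First-trimester visit:** a comparison of attenders with the baseline cannot separate earlier access from selective entry. The direction of any bias is not established.
- **Visit count:** the bias from women who could never enter the service favours the service. At an assumed 85% control rate it gives an odds ratio of 1.15 to 1.50 for 2% to 5% such women. The chance of a spurious favourable result is about 10% to 46% at the planned rural sizes, and about 9% to 40% after exclusions and missing data.

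The illustration assumes no service effect, attenders otherwise like controls, and no exclusion of zero-visit women. The true size cannot be determined from the protocol. Nothing here bears on the preterm-birth outcome for which the study is powered. This is a change worth making at low cost.

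**What to change.** **(a) First-trimester visit.** Base any claim of effect on a before/after comparison of all women having a First Nations baby at the site, whatever their model of care. Report attenders' figures as descriptive. The protocol already extracts these women: "Routinely collected data will be extracted for all women within the historical and intervention time periods who gave birth (or were booked to give birth"). The costs are dilution by women who did not use the service (on the indicative 26% uptake, an effect confined to users would shrink to roughly a quarter) and exposure to secular trend and COVID-19 over 2013–2022. The time trend should therefore be shown alongside.

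**(b) Visit count only.** Where the comparison by model of care is kept, restrict controls to women with at least one antenatal visit, and match or adjust for gestation at first visit. Do not apply this to the first-trimester outcome, because it would condition on that outcome. The cost is that any gain in visits that comes through earlier entry is left out.

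**(c) Minor: outcome 5.** Treat smoking at first visit as the baseline value. Analyse smoking after 20 weeks or at birth, already collected, as the outcome, adjusted for that baseline.

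All three are changes of analysis wording and need no new data collection.
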